### Aims

The main aims of this study are to:

1. Describe the evolution of early neurobehavioural development in infants <30 weeks from birth to two years’ CA compared with children born at term, and to explore how neurobehaviour is influenced by perinatal variables.

2. Explore the relationship between early neurobehavioural development and neonatal brain abnormalities (development and injury) at term using multi-modal MRI in infants <30 weeks at birth.

3. Investigate the predictive validity of neurobehavioural assessments during the early neonatal period for developmental outcomes at one and two years’ CA in infants <30 weeks at birth.

4. Examine symptoms of depression, anxiety, and post-traumatic stress in mothers and fathers of infants <30 weeks at birth and to describe changes in parental psychological wellbeing over the first two years of the child’s life compared with children born at term.

5. Examine parental psychological wellbeing, and parent and family factors during the neonatal period as predictors of development at one and two years’ CA in children born <30 weeks, and whether these relationships are similar in children born at term.

In addition, secondary aims of this study are to:

1. Explore whether neurobehavioural examinations in the preterm period relate to concurrent physiological status (i.e. heart rate and oxygen saturations) in infants <30 weeks at birth.

2. Describe the parenting beliefs and practices of parents of infants <30 weeks at birth across the first two years of the child’s life.

3. Examine whether parental psychological wellbeing from birth to one year CA is associated with the parent–child relationship and child development when the child is one and two years’ CA in infants <30 weeks at birth.

## Methods

### Design

Prospective observational cohort study.

### Study population

Preterm infants <30 weeks’ GA at birth admitted to one of the neonatal nurseries at the Royal Women’s Hospital in Melbourne, Australia. This project aims to recruit 150 infants <30 weeks at birth over a 3-year period from January 2011. A decision was made to focus on infants <30 weeks’ GA as this is the subgroup of children considered most at-risk of developmental problems. In addition 150 term-born children will be recruited from the Royal Women’s Hospital. This study has ethics approval from the Royal Women’s Hospital Ethics Committee.

### Inclusion/exclusion criteria for preterm infants

Inclusion criteria: Infants admitted to the Royal Women’s Hospital, Melbourne, Australia, neonatal nurseries, born <30 weeks’ GA. Exclusion criteria: (i) infants with congenital abnormalities known to affect neurodevelopment and (ii) infants with non-English speaking parents.

### Inclusion/exclusion criteria for term-born infants

Inclusion criteria: Infants admitted to the Royal Women’s Hospital Melbourne, Australia, born >36 completed weeks’ GA and weighing >2500 g. Exclusion criteria: (i) infants with congenital abnormalities known to affect neurodevelopment (ii) infants requiring admission to neonatal intensive or special care nursery and (iii) infants with non-English speaking parents.

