
### Project overview

This observational study will document the evolution of neurobehavioural development in very preterm infants (defined as <30 weeks gestation) and parental psychological wellbeing during the first two years of their child’s life using serial measurements from birth. The influence of perinatal variables and parental wellbeing on the neurobehavioural pathway will be examined, along with the relationship between early neurobehaviour trajectories and MRI findings at term equivalent age and developmental outcomes at one and two years’ CA. The relationships between parental psychological wellbeing, parent–child interaction and child developmental outcomes will also be described. A control group of infants born at term will also be recruited in the neonatal period to allow comparison in outcomes and to provide a local reference group.

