### Perinatal data collection

Following consent, the research nurses will collect maternal and perinatal data that are known to be related to neonatal and long-term outcome from medical histories. These data include pregnancy complications (e.g. pre-eclampsia) and treatments (e.g. magnesium sulphate), birth weight, sex, GA at birth, significant neonatal complications including grade of intraventricular haemorrhage, cystic periventricular leukomalacia, necrotising enterocolitis, culture positive infections and chronic lung disease, and the need for postnatal corticosteroids. A family questionnaire will be used to assess various sociodemographic factors including *The Social Risk Index*[37], which assesses 6 aspects of social status including family structure, education of primary caregiver, occupation of primary income earner, employment status of primary income earner, language spoken at home, and maternal age at birth. Also incorporated in this questionnaire will be items assessing parental alcohol and drug use, and mental health service access history which will be completed individually by mothers and fathers where possible.

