### Secondary aims

1. To explore whether the neurobehavioural trajectory varies according to concurrent physiological status, physiological status variables of interest will be dichotomised or separated into distinct categories (e.g. stable versus unstable). The mean (and 95% CI) scores at each time point (as described above) will be plotted separately for children within each category. Trends over time will be modelled using separate mixed effects regression models for each of the neurobehavioural scores including a fixed effect for time (gestational and chronological age) and physiological status and an interaction between time and physiological status to assess whether the effect of time is different in the different categories of this variable.

2. To describe the parenting beliefs and behaviour of parents of very preterm children across the first two years of the child’s life compared with term-born controls, we will present means and 95% CI for each parental assessment at each time point from term equivalent age to two years. Trends over time will be compared between the two groups using separate mixed effects regression models for each parent, with a fixed effect of time (gestational and chronological age) and group as well as an interaction between time and group. Models will also include a random effect to allow for repeated measures within a parent.

3. To examine whether parental psychological wellbeing is associated with the parent–child relationship when the child is one and two years’ CA, average scores for parental mental health from birth to 6 months, and from one to two years will be used as predictors of the 6 outcomes scales of the parent–child relationship measure at one and two years CA respectively. Separate linear regression models will be used for mothers and fathers to examine these relationships.

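### The only stated preterm-versus-term parent model has no covariates, so its group difference may be confounded by social risk and plurality

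*Protocol article*

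**What the plan says.** **Groups.** Preterm infants are those admitted to the "neonatal nurseries, born <30 weeks’ GA"; the exclusions are "infants with congenital abnormalities known to affect neurodevelopment and (ii) infants with non-English speaking parents". Nothing limits plurality or birth weight. Controls must be "born >36 completed weeks’ GA and weighing >2500 g", and the control exclusions add "infants requiring admission to neonatal intensive or special care nursery" to the same two rules on congenital abnormality and language. Study population says only that "In addition 150 term-born children will be recruited from the Royal Women’s Hospital". Recruitment has their families approached before discharge by the same method as preterm families. No matching is described.

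**Purpose of controls.** Project overview gives it as "to allow comparison in outcomes and to provide a local reference group".

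**Model.** Secondary aims, item 2 compares trends in parenting beliefs and behaviour between the groups. It uses mixed effects models with fixed effects of time and group "as well as an interaction between time and group", and a random effect for repeated measures within a parent. No other term is named.

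**Data available.** Perinatal data collection describes the Social Risk Index, "which assesses 6 aspects of social status including family structure, education of primary caregiver, occupation of primary income earner" among them. Table 5 collects it at birth, 12 and 24 months in both groups. Background lists social risk among the characteristics to be examined as predictors of continued parental distress. Plurality is not named among the perinatal data, but that list is introduced as examples and is not exhaustive.

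**The concern.** Readers are likely to take a preterm-versus-term difference in parenting as something that goes with very preterm birth. Two other features could contribute to it. Families of infants born before 30 weeks may differ in social background from term families who agree to take part. The preterm group may also contain more parents of multiples, because the weight and nursery rules apply to controls only. Both features could plausibly affect parenting competence and practices apart from gestation.

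The authors treat social risk as a possible predictor of parental outcome and measure it at birth in every family. Yet the one between-group parent model they write out does not use it. As specified, that model cannot show whether a difference remains once background and plurality are accounted for.

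**Working it through.** **1. The plan's own precision figure.** Sample size gives ±0.16 SD for a mean with 150 infants. Check: 1.960/√150 = 0.160. It reproduces, but it concerns one group's mean. No figure is given for a between-group contrast.

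**2. Precision of a between-group contrast.** For one visit with 150 parents of one sex per group, SE = √(2/150) = 0.115 SD. The minimum detectable difference at 80% power and two-sided 5% is (1.960 + 0.842) × 0.1155 = 0.32 SD.

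**3. Where an omitted baseline factor enters.** Let X be the factor, Δ its mean difference between the groups, c its constant effect on the score, and d its effect per unit of time. Leaving X out of the stated model has two consequences:
- the group difference in level is shifted by c × Δ;
- the time-by-group term is shifted by d × Δ.

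If X affects only the level (d = 0) and data are complete, the trend comparison is not biased. A simulation with three complete visits, Δ = 0.4 SD and c = 0.25 agreed. The unadjusted level difference was off by 0.4 × 0.25 = 0.10 SD, and the interaction estimate was the same with and without X.

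**4. Possible size of the level bias.** The documents give neither Δ nor c. For a yes/no factor, bias = (prevalence difference) × (effect in SD). The rejection rate of a nominal 5% test with no true difference is 1 − Φ(1.960 − bias/0.1155) + Φ(−1.960 − bias/0.1155). All inputs below are assumptions:

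| Prevalence difference | Effect (SD) | Bias (SD) | Rejection rate |
|---|---|---|---|
| 0.1 | 0.2 | 0.02 | 5.3% |
| 0.3 | 0.3 | 0.09 | 12.2% |
| 0.3 | 0.5 | 0.15 | 25.5% |
| 0.4 | 0.5 | 0.20 | 41.0% |

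These rates are for a single cross-sectional contrast, not for the trend test. If both members of a twin pair are enrolled, there are fewer preterm families than infants; the SE rises a little and the rates fall slightly.

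**5. Do the control criteria remove multiples?** The documents contain no twin weights. If term twins averaged 2400 to 2700 g with SD 350 to 400 g (assumed), the share of individual twins above 2500 g would run from 1 − Φ(100/350) = 39% to 1 − Φ(−200/400) = 69%. The weight rule would then thin out multiples without eliminating them. The effect of the nursery rule cannot be calculated.

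**The case against.** The strongest case against has four parts.

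- **Covariates may be in an analysis plan that is not shown.** This is possible. But the article sets out the fixed and random effects of this model, and where its authors want several factors considered jointly (main aim 5) they say so. The point concerns a stated model, not an omitted detail.
- **The aim is descriptive, and the controls are a local reference group.** This stands. An unadjusted difference is a legitimate answer to a descriptive aim, so the stated model should be kept and labelled as such. The documents do not say that the group effect is to be read causally.
- **The model compares trends, and a covariate entered only as a main effect leaves the trend term essentially unchanged.** This also stands, as step 3 shows. Any adjustment meant to reach the trend must include the covariate's interaction with time.
- **Nothing shows that the groups differ.** No eligibility rule concerns social status as such, the language exclusion is the same in both groups, and hospital and approach are shared. This stands as far as it goes. Lack of matching leaves balance uncontrolled; it does not show imbalance.

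A reader might infer from the weight and nursery rules that twins are in effect excluded from the controls. The documents do not support that: they set no plurality rule and give no figures. Under-representation of multiples is probable, but it is an inference.

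**Conclusion.** The point holds as a possibility of confounding in a stated model. The group difference in level from Secondary aims, item 2 may be confounded by social risk and plurality. The trend difference may be too, but only if those factors influence change over time. The weakness lies in the model, not in the eligibility criteria, which suit a healthy term reference group.

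The size is unknown. Under the assumed ranges it runs from negligible (0.02 SD) to material (0.20 SD, against a minimum detectable difference of 0.32 SD). A reader might go further, add both sources in the same direction near the top of assumed ranges to reach about 0.25 SD, and conclude that a nominal 5% test would reject 58% of the time. That arithmetic is correct for SE 0.115, but no document figure supports the inputs and it does not describe the trend test. It should not be quoted as the study's error rate.

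The change is worth making because social risk is already collected in both groups and the authors themselves regard it as a candidate predictor.

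**What to change.** In Secondary aims, item 2:

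1. Keep the stated model and report it as the unadjusted, descriptive contrast.
2. Beside it, report an adjusted version with the birth Social Risk Index and multiple birth (yes/no, from the birth record) as fixed effects. Where trends are compared, add the interaction of each with time.
3. If controls include few multiples, the plurality coefficient would be estimated almost wholly within the preterm group. In that case report a singleton-only sensitivity comparison instead of relying on that covariate.
4. State that plurality is recorded in both groups.

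The cost is slightly wider intervals, particularly in the singleton-only comparison, and a little more analysis work. The Social Risk Index needs no new collection, and the eligibility criteria and recruitment stay as they are.

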### Recruitment

A research nurse will approach eligible families of very preterm children within the first or second week of life, following approval from the medical team. The research nurse will verbally explain the study, including the time commitment and give written information on the study. Both parents will be invited to be in the study. If the parent/s agree to be in the study they will be asked to sign a consent form. Families of term-born infants will be approached by a research nurse prior to discharge following the same methodology as above.

### Perinatal data collection

Following consent, the research nurses will collect maternal and perinatal data that are known to be related to neonatal and long-term outcome from medical histories. These data include pregnancy complications (e.g. pre-eclampsia) and treatments (e.g. magnesium sulphate), birth weight, sex, GA at birth, significant neonatal complications including grade of intraventricular haemorrhage, cystic periventricular leukomalacia, necrotising enterocolitis, culture positive infections and chronic lung disease, and the need for postnatal corticosteroids. A family questionnaire will be used to assess various sociodemographic factors including *The Social Risk Index*[37], which assesses 6 aspects of social status including family structure, education of primary caregiver, occupation of primary income earner, employment status of primary income earner, language spoken at home, and maternal age at birth. Also incorporated in this questionnaire will be items assessing parental alcohol and drug use, and mental health service access history which will be completed individually by mothers and fathers where possible.

## Child assessments

### Serial neurobehavioural assessments up to term (preterm infants only)

There is no single assessment tool, with good reliability, that has been validated for use prior to term equivalent age to assess neurobehaviour from birth [2]. Therefore, we will use four assessment tools in this study, the NICU Network Neurobehavioral Scale (NNNS) [38], the Hammersmith Neonatal Neurological Examination (HNNE) [39], Prechtl’s assessment of General Movements (GMs) [40] and the Premie-Neuro (Table 1) [41]. The NNNS and HNNE have been validated for use at term equivalent age, however, there are many items that are not appropriate for more preterm and medically unstable infants, for example “pull to sit” or “following an object”. We will therefore need to exclude or modify these items for the assessment of infants at earlier GAs. GMs and the Premie-Neuro are appropriate for use from preterm birth and will not be modified. In addition to these standardised assessments, we will develop a new assessment tool to measure neurobehaviour, which will involve observation of the infant’s behavioural cues during regular care procedures and the neurobehavioural assessments.

**Table 1 T1:** Description and purpose of neurobehavioural assessments

**Assessment**	**Purpose**
NNNS [38]	The *Neonatal Intensive Care Unit Network Neurobehavioral Scale* (NNNS) assesses the neurological integrity, behavioural functioning, and responses to stress in high-risk infants using 45 items compared with norms for healthy term infants (n = 125). The NNNS provides an in-depth assessment of neurobehaviour and gives summary scores/subscales for attention, handling, quality of movement, regulation, nonoptimal reflexes, arousal, hypertonicity, hypotonicity, asymmetrical reflexes, excitability and lethargy.
HNNE [39]	The *Hammersmith Neonatal Neurologic Examination* (HNNE) consists of 34 individual items with 6 subtotals including tone, tone patterns, reflexes, spontaneous movements, abnormal neurological signs and behaviour in newborns. It provides an overall “optimality score” which has been validated in healthy term (n = 224) and preterm (n = 380) infants. This assessment tool is used frequently in clinical practice and requires no formal training.
GMs [40]	Prechtl’s *General Movements* (GMs) assessment is a non-invasive method for assessing global neurological development, particularly motor development. Video recordings are made of spontaneous whole body movements and assessed at a later time by independent assessors. GMs during the neonatal period have been shown to be predictive of cerebral palsy from birth in the preterm infant. This assessment has the advantage of obtaining an overall picture of neurological integrity without needing to handle the infant.
Premie-Neuro [41]	The Premie-neuro is a brief neurological examination for preterm infants aged 23–37 weeks’ gestation. Consists of 24 items divided into neurological, movement and responsiveness subgroups. Validity has been shown in a small study (n = 34), however the inter-rater reliability was low.

Each examination will be video-recorded so that assessments can be scored later as appropriate. As infants prior to term age in the NICU can be sensitive to handling we will not administer any item considered to cause the infant unnecessary stress. During the assessment, we will simultaneously observe pulse oximetry data, which will give information on oxygen saturations and heart rate. If these data and other behaviour, such as apnoea, suggest increased stress levels in the infant as a result of the neurobehavioural assessment, administration of that item will cease. The assessment will be continued where possible. Due to the poor self-regulation abilities and sensitivity to handling of infants younger than 30 weeks’ GA, it will be necessary for early evaluations (<30 weeks’ GA) to principally involve observation, focusing on: GMs [40], state, motor and autonomic regulation and the infant’s response to external stimuli. Behavioural (e.g. colour changes, facial expressions) and motor observations (e.g. postural tone and quality of spontaneous movements) will be video-recorded during a standard care procedure (e.g. a nappy change) to evaluate the infant’s response to handling during an everyday activity. The video recordings will allow the assessor to make more detailed assessments than they are able to do in real-time and allow for inter-observer reliability of scoring (two scorers will be used to assess reliability). Evaluations will be completed weekly from enrolment up to 32 weeks’ GA, then fortnightly until term, or discharge from the Royal Women’s Hospital. Assessments will be timed to coincide with care procedures to ensure the infants’ sleeping patterns are not disrupted. Initially assessments will take approximately 15 minutes and increase to 30 minutes as the infants become older and more stable, enabling us to elicit more specific responses.

To standardise the assessment procedure in the neonatal nursery, we will assess the infant in an environment with minimal lighting and low noise levels. The assessors will be health professionals (e.g. physiotherapists, occupational therapists, nurses and physicians) who have received training in the neurobehavioural assessment and who are not involved with the clinical care of the child. All assessors will have accreditation for the relevant assessment tools where required (i.e. NNNS and GMs). The assessors will liaise closely with the clinical team, particularly the bedside nurse, to time the assessment with the baby’s care to minimise handling.

### Assessment at term equivalent age (both preterm and term infants)

#### Serial neurobehavioural assessments

At term equivalent age (38–44 weeks’ GA) infants will have neurobehavioural assessments carried out by an independent assessor blinded to previous examination results and clinical history (including prematurity). The term neurobehavioural assessment will consist of the NNNS, followed by the additional items needed to complete the HNNE (i.e. reflexes, arm and leg recoil) and five minutes of video footage for GMs of the infant in an active or quiet alert state.

#### Magnetic resonance

The MRI scan is not a compulsory component of the study and parents consenting to the study can choose for their baby not to have the MRI scan. For those who consent, MRI scans will be performed without anaesthesia or sedation, between 38–44 weeks’ GA on the same day as the term equivalent age neurobehavioural assessment. All scans will be performed at the Royal Children’s Hospital using the 3 T Siemens Magnetom Trio MRI scanner. The scanning session will take approximately 60 minutes. A full anatomic, functional, developmental and metabolic infant brain MRI study will be performed using the following sequences:

•**T2-weighted images:** Transverse Restore turbo spin echo imaging: Flip angle = 120, Repetition Time = 8910 ms, Echo Time = 152 ms, Field Of View = 192 × 192 mm, Matrix = 192 × 192, 1 mm [3] isotropic voxels.

•**T1-weighted images:** Transverse multi-planar reconstruction imaging with noise suppression: Flip angle = 9°, Repetition Time = 2100 ms, Echo Time = 3.39 ms, Field Of View = 192 × 192 mm, Matrix = 192 × 192, 1.0 mm [3] isotropic voxels.

•**Diffusion weighted imaging:** Transverse echo planar imaging: Repetition Time = 20400 ms, Echo Time =120 ms, Field Of View =173 × 173 mm, Matrix = 144 × 144, 1.2 mm [3] isotropic voxels, 45 gradient directions (range b = 100 to b = 1200s/mm [2]), 3 b = 0 s/mm [2].

•**Resting state functional connectivity MRI:** Transverse 2D echo planar imaging with prospective acquisition correction: Repetition Time = 2910 ms, Echo Time = 28 ms, flip angle = 90°, Field Of View = 151 × 151 mm, Matrix = 64 × 64, 2.4 mm [3] isotropic voxels.

•**Proton magnetic resonance spectroscopy:** Transverse spin echo chemical shift imaging: Repetition Time = 2000, Echo Time = 135, flip angle = 90°, scan resolution = 12 × 12, interpolated 16 × 16, field of view = 103 × 125 mm, voxel size = 10.4 × 8.6 × 15.0 mm.

The MRI scans will be qualitatively evaluated by two independent investigators who are blinded to the clinical neurobehavioural assessment, utilising an established scoring method for newborn infants [42]. This scoring system provides an overall measure of the presence and severity of white matter, cortical grey matter, deep grey matter and cerebellar abnormalities (recorded as normal, mild, moderate, or severe). Quantitative image analysis will involve the following image analyses:

•**Structural T1-weighted and T2-weighted MR image analyses:** Grey and white matter and cerebrospinal fluid will be initially segmented using SPM8 software (http://www.fil.ion.ucl.ac.uk/spm/software/spm8) with tissue priors from a 40-week neonatal template [43], and then fed into a modified version of a previously published morphology-driven automatic segmentation pipeline [44] to obtain volumes of white matter, cortical grey matter, cerebrospinal fluid, deep nuclear gray matter, brainstem, hippocampus, amygdala and cerebellum [19]. These assessments will enable an assessment of size and morphological alterations to global and regional areas of the brain.

•**Diffusion imaging and tractography:** Vulnerable white matter fibre bundles of the visual, motor, language and attention pathways will be isolated by tractography. Diffusion tractography enables the characterisation of particular fibre tract populations which can then be related to early neurobehavioural functions. Tract-specific diffusion measures of fractional anisotropy, mean diffusivity, axial and radial diffusivity will be calculated. Diffusion measures provide insight into white matter tissue integrity reflecting microstructural organisation, water content, number and density of axons, and myelination, and are useful for gauging white matter maturity [45,46]. Structural connectivity will also be performed, where white matter fibre networks will be analyzed using graph theory metrics [47].

•**Resting state functional MRI:** Resting state functional connectivity (fcMRI) will be assessed by detecting temporal correlations in spontaneous blood oxygen level dependent (BOLD) signal oscillations while subjects rest quietly in the scanner. Distinct resting-state networks related to vision, language, executive processing and other sensory and cognitive domains will be identified. This will allow relationships between specific neurodevelopmental impairments and functional brain networks to be determined [48].

•**Proton magnetic resonance spectroscopy:** Brain metabolites in specific brain regions will be measured using proton MR spectroscopy. Measurements will be made for (a) N-acetyl aspartate, which is reduced as a result of destruction of neurons or decreased neuronal integrity (b) Lactate, which is elevated in regions where cell and tissue necrosis have occurred (c) Choline which reflects cellularity and is elevated in response to demyelination and gliosis (d) Glutamine and glutamate, markers for neuronal damage, and (e) myo-inositol, a marker for myelin breakdown. Levels of these markers, in regions of interest from the frontal and occipital white matter will be important to elucidate the association between neurobiological abnormalities as a result of hypoxic ischaemic events or infection/inflammation and adverse early neurobehavioural characteristics.

